#### Home Visit Intervention Group

Home visits are considered the gold standard for enhancing child health and development in LMICs [21]. Families in the home visit intervention group (home visit group) receive support through biweekly home visits following the nationally developed and validated curriculum of the national ECD program PNCM. The PNCM program offers home visits to low-income families residing in rural areas (*Servicio de Acompañamiento a Familias*) and daycare services in urban settings (*Servicio de Cuidado Diurno*) [23]. Specifically, all families in the home visit group are receiving biweekly home visits by our trained field staff from when their children turn 6 months until endline assessments at approximately 2.5 years of age. Trained staff members visit families at home every 2 weeks. During these visits, they follow a structured (age-specific) curriculum to educate parents on engaging in educational activities and games for daily interaction with their children, actively play with the child, and provide parents with a set of age-appropriate toys every 3 months. The toys and activities were designed in Peru to promote their children’s psychomotor, cognitive, language, and socioemotional development.

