### Sample Size Calculations

The study is powered to detect a 0.25 SD difference in normalized child development *z* scores (mean 0, SD 1) at the age 2 years between the Afini group and the control group and a difference of 0.5 SD in *z* scores between the home visit group and the control group. These calculations are based on the following assumptions: (1) an average of 15 (SD 5) children per village or study cluster, (2) an intraclass correlation of 0.12, (3) α=.05, and (4) an attrition rate of 15%. The estimated normalized effect size of 0.5 SD was based on 2 recent reviews of ECD home visiting programs [10,16]. We conservatively anticipate the Afini platform to only reach about half the target population and, thus expect an intention-to-treat effect size of 0.25 SD. Our assumptions regarding intraclass correlations, number of children per cluster, and attrition rates are based on a recently completed ECD-focused study in the same area [17].

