### Recruitment

Recruitment occurred continuously over 18 months with a target to enroll 2460 caregiver-child dyads. To identify potential children, the local health facilities’ birth registries from San Marcos, Cajamarca, and Cajabamba were used. All children between 3 and 9 months of age identified during the recruitment period in the study catchment area were eligible. All families that complied with the eligibility criteria were visited in person by study staff and invited to participate. The only reasons for exclusion were if the (1) caregiver and child intended to migrate outside the study area within the next 12 months, (2) child had a diagnosis of congenital abnormalities or a disability such as deafness or blindness (as reported by the caregiver), and (3) child already participated in the national PNCM program and did not belong to the PNCM comparison group. The study was built on a long-standing relationship of the research team with the regional and local health centers that facilitated recruitment.

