### Primary and Secondary Outcome Measures

The primary study outcome will be children’s overall development at the age of 2.5 years. Children’s development will be assessed using the long form of the Global Scales for Early Development (GSED) [38]. The GSED is a new global open access tool designed to provide a standardized method for measuring the development of children up to 36 months of age in low-resource settings. We will use the long form of the GSED tool, which allows for a direct assessment of children’s development through trained assessors.

Secondary outcomes include (1) caregiver-reported early child development in motor, cognitive, language, and socio-emotional domains; (2) quality of a caregiver-child relationship; (3) screen time with and without a child being present; (4) primary female caregiver’s parenting behaviors; (5) parenting attitudes; and (6) mental health. Table 1 summarizes the measures to be collected at baseline and endline—all measures will be applied to the full sample, that is, to all participants independent of their random group assignment. Given that children were very young at baseline (6 months on average), detailed assessments of child development and caregiver-child interactions seemed unlikely to yield much insight at baseline. For overall child development, we used a caregiver report (Caregiver Reported Early Development Instruments [39]) at baseline and will use a more detailed direct observation tool (GSED) at endline. Sociodemographic factors collected at baseline will be used as controls in the final analysis.

**Table 1 table1:** Overview of constructs and measures used at baseline and endline.

Construct and measures		Time of assessment

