#### End-of-Study Assessments

The endline surveys will occur when children reach 2.5 years of age, which will begin in September 2023. Table 2 shows an overview of the study timeline.

**Table 2 table2:** Study timeline and project activities.

Time period	Description of project activities
July 2020 to January 2021	Study setup, software development, and ethics board approval
February to July 2021	Field testing and finalizing tool development and high-frequency feedback to the programming team
September 2021 to March 2023	Enrollment and baseline survey of 2471 small children and their caregivers in the main trial plus 237 small children and their caregivers in the comparison group (total 2708 project participants)
September 2021 to August 2024	Parenting interventions
August 2023 to September 2024	Endline survey and assessments
October 2024 to February 2025	Data analysis
March 2025	Study dissemination event

The end-of-study assessment will involve gathering information on child development, maternal mental health, mother-child interactions, and parenting attitudes toward the child. To measure the primary outcome, we will use the GSED assessment tool [38]. Secondary outcomes include (1) caregiver-reported early child development in motor, cognitive, language, and socioemotional domains; (2) the quality of a caregiver-child relationship; (3) screen time with and without the child being present; (4) primary female caregiver’s parenting behaviors; (5) parenting attitudes; and (6) mental health. Table 1 provides details on the instruments used.

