### Home Visits

For each home visit, a short visit form was completed to document the time and date, topics covered, and toys delivered. Additionally, we collected information about the play environment, the toys available, and the interactions between the caregiver and the child at the time of the visit.

Table 3 provides an overview of all study activities. Recruitment and baseline surveys started in the third quarter of 2021. Given the prerandomization of clusters to treatment, interventions were initiated directly after baseline in September 2021, gradually increasing sample sizes in all arms. Recruitment was completed in January 2021, and the first households were scheduled to complete the endline assessment (and exit the study) in September 2023. Interventions will continue (with a steadily decreasing number of households) until the last household completes the endline survey and exits the study in late 2024.

**Table 3 table3:** Overview of study activities^a^.

Study activity		Year and quarter																		
		2021					2022					2023					2024			
		1	2	3	4	1		2	3	4	1		2	3	4	1		2	3	4

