### Statistical Analysis

After confirming the psychometric reliability and validity of our key variables, we will perform a descriptive analysis (means and percentages) for the main characteristics and calculate prevalence and proportions for the primary outcomes. We will use standard linear regression models to assess the impact of the 2 intervention arms on child development. The primary outcome variable will be overall development as measured by the GSED, normalized to a developmental *z* score with a mean (0, SD 1) in the global reference population. Our primary empirical approach will be intent-to-treat, that is, comparing average outcomes across the 3 arms (independent of intervention compliance) with average outcomes in the control group. We will also conduct additional per-protocol analyses measuring mean differences between compliant children in the intervention arms with compliant children in the control group. For the home visit group, compliance will be defined as receiving at least 18 out of the 36 anticipated visits over the 18-month intervention period. Compliance with the Afini intervention will be defined as having interacted with the system at least once per month for at least 6 months in the observation period. Cluster-robust standard errors will be used to account for the cluster-level randomization of the intervention. Separate models will be estimated with and without baseline covariates.

Specifically, we will assess and control for household factors, caregiver factors, and child factors. Structural equation modeling will be used to test subgroup and mediation effects.

We will calculate the intervention’s cost-effectiveness by comparing the developmental outcomes observed in the 2 intervention arms to the average developmental levels in the control arm to the costs of the 2 interventions per child.

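### Home-visit compliance is set at 18 of 36 visits over 18 months, but the described schedule runs 24 months with 48 to 52 visits, so at full exposure 18 visits is about 35% to 38%, not half

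*Protocol article*

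**What the plan says.** The Statistical Analysis section of the protocol article makes intent-to-treat the primary approach and adds per-protocol analyses. For the home visit group, "compliance will be defined as receiving at least 18 out of the 36 anticipated visits over the 18-month intervention period".

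The Home Visit Intervention Group section describes a longer intervention. All families in that arm receive "biweekly home visits by our trained field staff from when their children turn 6 months until endline assessments at approximately 2.5 years of age", and the frequency is restated: "Trained staff members visit families at home every 2 weeks".

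The 2.5-year endpoint recurs. The primary outcome is "overall development at the age of 2.5 years", and under End-of-Study Assessments, "The endline surveys will occur when children reach 2.5 years of age". The Home Visits section adds that interventions continue, with fewer and fewer households, until the last household has completed endline. The one place that uses an earlier age is Sample Size Calculations, where the detectable difference is set "at the age 2 years between the Afini group and the control group".

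**The concern.** The compliance rule and the intervention description give different lengths for the same intervention. The rule's denominator of 36 belongs to an 18-month period, whereas the described schedule runs from 6 to 30 months of age. No sentence presents 18 months as a minimum, an average or a special case; the rule speaks of a single intervention period for the arm.

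What is at stake is how the per-protocol home-visit result is read. Written as 18 out of 36, the threshold tells readers that a compliant family received at least half of what was planned. If the plan was 48 to 52 visits, a family with little more than a third of them qualifies. And if exposure differs with enrolment date, one fixed count stands for different levels of adherence within the same analysis set.

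**Working it through.** **Inputs from the article**
- Threshold 18 visits, denominator 36, period 18 months (Statistical Analysis).
- Visits from age 6 months to about 30 months, one every 2 weeks (Home Visit Intervention Group).
- Enrolment age: "All children between 3 and 9 months of age identified during the recruitment period in the study catchment area were eligible". Mean baseline age in the home-visit arm is 5.1 months (Table 4).
- Enrolment from September 2021 to March 2023; endline from August 2023 to September 2024 (Table 2).

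**Formulas.** Visits = 2 × months (two per month), or months × 30.4375 / 14 (strict 14-day spacing). Share = 18 / visits.

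**The plan's own figure.** 18 months × 2 = 36, and 18/36 = 50%. This reproduces, but only with 18 months and two visits per month. Strict 14-day spacing over 18 months gives 39.1 visits.

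**The same threshold under the described schedule**

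| Case | Months | Visits, two per month | Visits, every 14 days | 18 visits as a share | Half the schedule |
|---|---|---|---|---|---|
| Rule as written | 18 | 36 | 39.1 | 50.0% to 46.0% | 18 to 19.6 |
| Full exposure, 6 to 30 months of age | 24 | 48 | 52.2 | 37.5% to 34.5% | 24 to 26.1 |
| Enrolled at 9 months, followed to 30 | 21 | 42 | 45.7 | 42.9% to 39.4% | 21 to 22.8 |
| Enrolled March 2023 at 5.1 months, endline September 2024 | 17.1 | 34.2 | 37.2 | 52.6% to 48.4% | 17.1 to 18.6 |

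The last row is 18 calendar months (March 2023 to September 2024) less the 0.9 months until the child turns 6 months (6 − 5.1). A child already 6 months or older at a March 2023 enrolment has the full 18 months, as in the first row. A child enrolled that month at 3 months would have 18 − 3 = 15 months, or 30 to 32.6 visits, and 18 would be 60% to 55%.

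**Which case is usual?** The mean baseline age lies below the 6-month start of visits, so age at enrolment does not shorten the 24 months for an average child; only the calendar can. Such a child reaches 30 months 24.9 months after baseline (30 − 5.1) and so completes the schedule by the end of September 2024 if enrolled by about early September 2022. If enrolment was even over about 19 months (an assumption; the article does not give the pattern), about 12 of those 19 months fall before that date. Roughly a third of families then could not have the full 24 months.

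The end date itself varies within the article. With interventions ending in August 2024 (Table 2) the fraction cut short is about 8/19, or two fifths. If the late 2024 of the Home Visits section is read as December, it is about 4/19, or a fifth. On each reading, most families have the full schedule.

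**The case against.** The best defence is that the rule works as it stands. Its internal arithmetic is right, and a fixed dose of 18 visits can be counted from the visit forms. The Afini rule beside it is also a fixed amount of use (monthly interaction for at least 6 months). The text never says that the aim is half of each child's own schedule. The calendar also gives 18 months a plausible meaning, since it is the gap between the last enrolment and the close of endline, and for those children 18 visits is about half.

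Much of this stands. A fixed count is a legitimate choice, and a reader who inferred that 50% is wrong for every family would go too far. What does not stand is the denominator. The article gives 36 visits and 18 months as the anticipated programme for the whole arm, not as the minimum exposure of its latest enrolees, and its own intervention description says otherwise.

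Three stronger readings are tempting but unsupported.
- That the 18 months is left over from an endpoint at age 2 years: 6 to 24 months is 18 months, so it fits, but the article does not say so.
- That the per-protocol effect will be biased in a known direction: the article gives no basis for one, nor for how many families would change status.
- That the main result is compromised: the primary comparison ignores compliance.

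Leaving detail to an analysis plan is not an answer here, because the article states the period and count and they conflict with its own schedule.

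**Conclusion.** The point holds as an inconsistency between the compliance rule and the intervention description. At full exposure, 18 visits is about 35% to 38% of the described schedule, and half would be 24 to 26 visits, 6 to 8 more than the rule asks. The lower share, full exposure for most families and the move to about half for the latest enrolees together mean that the set would be described as more adherent than it is, with the meaning of compliant depending partly on enrolment date.

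The percentages rest on reading the schedule as two visits per month up to one every 14 days, and on endline at 30 months unless the September 2024 close intervenes. The statement that most families have full exposure further assumes roughly even enrolment.

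The consequence is limited to the additional per-protocol analysis of the smallest arm (316 of 2471 dyads). It is worth correcting because the figure defines an analysis set, is wrong as written, and is cheap to put right.

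**What to change.** Correct the intervention period and anticipated visit count in the Statistical Analysis section to match the intervention description: 24 months and 48 to 52 visits at full exposure. That is the firm part.

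Then choose how to state the threshold.
- To keep the 50% ratio, define compliance as at least half of the visits scheduled between each child's start (the later of baseline and age 6 months) and that child's endline date. Report the fixed count of 18 as a sensitivity analysis.
- If the fixed count stays as the main rule, describe it as about 35% to 38% of the full schedule.

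The cost is one or two sentences and no new data, since "For each home visit, a short visit form was completed to document the time and date, topics covered, and toys delivered". The small downside of the proportional rule is that absolute dose among compliers then varies with exposure time, which the fixed-count sensitivity analysis covers.

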### Study Design

The study was designed and adapted based on a field-testing phase completed over a period of 5 months from February to July 2021. During the test phase, we conducted a mixed method feasibility pilot to test the reach, reception, and use of the Afini parenting platform. Specifically, we (1) systematically assessed internet connectivity in the greater study region, (2) conducted focus groups and in-depth interviews to adapt Afini to the local cultural context, and (3) assessed use over time and satisfaction with Afini in a sample of 280 mothers with children up to 2 years of age and smartphone access [35].

The study was designed as a 3-arm parallel cluster randomized controlled trial to assess the Afini platform’s effectiveness in improving ECD outcomes relative to a control group receiving no additional intervention as well as relative to a home visit group receiving an ECD home stimulation intervention (gold standard). The trial enrolled 2471 caregivers and their 3- to 9-month-old children across 164 community clusters from September 2021 to March 2023. As described above, communities were randomly assigned to the three study groups: (1) a control group receiving no additional ECD support (72 community clusters and 980 caregiver-child dyads), (2) a home visit intervention group receiving a biweekly home visit by a trained field staff following the national ECD program PNCM curriculum and training guidelines (20 community clusters and 316 caregiver-child dyads), and (3) the Afini intervention group receiving ECD activities and advice through the digital Afini platform (72 community clusters and 1175 caregiver-child dyads).

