### Randomization Process

Stratified constrained randomization was used to ensure both spatial and covariate balance across groups. As study strata, 3 study provinces (Cajamarca, Cajabamba, and San Marcos) were used. Within each stratum, communities were allocated with ratios 3.6:1:3.6 for the control group, home visit group, and the Afini group, resulting in a final sample of 72 clusters in both the control group and Afini group and 20 clusters in the home visit group. A total of 1000 potential cluster allocations were randomly drawn using the Stata SE (version 16.0; Stata Corp) software package. We then chose the allocation minimizing mean differences across the 3 arms concerning variables such as cluster population size, cluster number of births, cluster altitude, household cell phone ownership, education of caregiver, and household wealth. Information on these covariates was obtained from governmental sources and validated by our field staff.

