## Results

As shown in Table 2, enrollment and baseline data collection were completed in March 2023, and endline assessments were launched in September 2023. Table 4 shows descriptive statistics for the baseline sample by study arm. On average, children were 5 months old at baseline, 49.9% (1223/2452) were female, 8.1% (199/2452) had low birthweight (<2500 g at birth), and 97.5% (2391/2452) of children had a child health card. On average, mothers were 28 years old and considered literate. Fathers were slightly older, with an average age of 31.5 years at baseline, and had slightly higher education levels than mothers. The average household consisted of 2.5 adults and 1 additional child (sibling).

**Table 4 table4:** Descriptive statistics.

Characteristics	Control (n=962)				Home visits (n=315)				Afini (n=1175)		
	Observations, n	Clusters, n	Mean (SE)	Observations, n		Clusters, n	Mean (SE)	Observations, n		Clusters, n	Mean (SE)
Child age (months)	959	67	5.0 (0.11)	315		19	5.1 (0.22)	1169		78	5.1 (0.10)
Child is female	954	67	0.51 (0.02)	314		19	0.48 (0.03)	1172		78	0.50 (0.01)
Child has a health card	959	67	0.98 (0.01)	315		19	0.97 (0.01)	1169		78	0.98 (0.01)
Child born <2500 g	949	67	0.08 (0.01)	308		19	0.10 (0.02)	1152		78	0.08 (0.01)
CREDI^a^ score	950	67	43.0 (0.066)	307		19	43.0 (0.163)	1163		78	43.2 (0.065)
Mother’s age (years)	945	67	27.7 (0.26)	311		19	28.6 (0.48)	1155		78	28.0 (0.22)
Mother is literate	941	67	0.98 (0.01)	307		19	0.97 (0.01)	1151		77	0.99 (0.004)
Mother education level	944	67	3.2 (0.08)	310		19	3.2 (0.23)	1154		78	3.4 (0.08)
Father’s age (years)	843	66	31.2 (0.26)	277		18	32.1 (0.52)	1027		76	31.6 (0.26)
Father is head of household	844	66	0.94 (0.01)	277		18	0.94 (0.02)	1026		76	0.94 (0.01)
Father education level	832	66	3.5 (0.07)	267		18	3.5 (0.22)	1007		76	3.7 (0.07)
SES^b^ index	957	67	2.9 (0.12)	315		19	3.1 (0.29)	1169		78	3.2 (0.12)
Stimulation index	868	66	3.4 (0.06)	285		19	3.4 (0.14)	1076		78	3.5 (0.06)

^a^CREDI: Caregiver Reported Early Development Instruments.

^b^SES: socioeconomic status.

We anticipate completing the endline assessments in September 2024 and presenting final trial results to the local and national governments in Peru in early 2025.

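### With 19–20 home-visit clusters, the usual cluster-robust test of the home-visit contrasts has a type I error of about 6–7% instead of 5%; a few-cluster correction should be named

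*Protocol article*

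**What the plan says.** Statistical Analysis names the model, "We will use standard linear regression models to assess the impact of the 2 intervention arms on child development", and the variance method, "Cluster-robust standard errors will be used to account for the cluster-level randomization of the intervention". It adds: "Separate models will be estimated with and without baseline covariates". It does not give the variant of the robust variance, the reference distribution or the degrees of freedom. The covariates it lists are household, caregiver and child factors. Province and the cluster-level balancing variables are not named there.

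Randomization Process gives the cluster numbers: "resulting in a final sample of 72 clusters in both the control group and Afini group and 20 clusters in the home visit group". It also says that the best-balanced of 1000 random allocations was chosen, within province strata. Study Design gives the home-visit arm as "20 community clusters and 316 caregiver-child dyads". Table 4 in Results shows 67, 19 and 78 clusters for control, home visits and Afini; both sets sum to 164.

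Sample Size Calculations assumes "an average of 15 (SD 5) children per village or study cluster" and "an intraclass correlation of 0.12", with α=.05 and 15% attrition.

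**The concern.** A trial with 164 clusters looks large enough for the ordinary sandwich variance. But precision for the home-visit coefficient is limited by its own arm, which has 19 or 20 clusters. Two things then go wrong together. The uncorrected sandwich underestimates that arm's variance by a factor of about (K−1)/K, and a t distribution on 163 degrees of freedom is too narrow when the effective number is about 30.

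Home visits versus control is one of the two comparisons for which the study is powered. The home-visit arm is also the gold standard against which Afini is judged. If its intervals are too narrow, the benchmark and the Afini-versus-home-visit comparison look more certain than they are.

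**Working it through.** **Step 1. The plan's own figures.** 164 clusters × 15 = 2460, the stated enrolment target. For power, 15% attrition gives m = 15 × 0.85 = 12.75, and CV = 5/15 = 0.33. The design effect is 1 + [(1 + CV²)m − 1] × ICC = 1 + [1.111 × 12.75 − 1] × 0.12 = 2.58.
- Home visits v control: SE = √[2.58/12.75 × (1/72 + 1/20)] = 0.114; power at 0.5 SD = Φ(0.5/0.1137 − 1.96) = 99.3%.
- Afini v control: SE = √[2.58/12.75 × (2/72)] = 0.0750; power at 0.25 SD = Φ(0.25/0.0750 − 1.96) = 91.5%.

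The power claim is met. The question is only whether the test holds its level.

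**Step 2. Closed form, equal cluster sizes, no covariates.** For home visits (20) v control (72), with the usual G/(G−1) factor of 164/163:
- Home-visit share of the contrast variance: (1/20)/(1/72 + 1/20) = 78%.
- Expected estimated variance ÷ true variance: (71/72² + 19/20²) × (164/163)/(1/72 + 1/20) = 0.964.
- Satterthwaite df: (1/72 + 1/20)²/[(1/72²)/71 + (1/20²)/19] = 30.4.
- True rejection rate: the t(163) critical value is 1.975, and 2·P(t₃₀.₄ > 1.975 × √0.964) = 2·P(t₃₀.₄ > 1.938) = 6.2%.
- Interval width: 2.041/1.938 = 1.053, so intervals should be about 5% wider.

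With the Table 4 counts (67 and 19), the ratio is 0.962, the df 29.0 and the rate 6.3%. If all the variance came from the home-visit arm, the rate would be 6.9% (20 clusters) or 7.0% (19 clusters). For Afini v control (72 v 72), the same formulae give ratio 0.992, df 142 and 5.1%.

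**Step 3. Simulation, no covariates.** ICC 0.12, normal outcomes, null true, two-sided 5%, 20,000 trials per row (Monte Carlo SE about 0.2 points). CR1 is the usual sandwich, referred to t(163).

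| Clusters; size | Home visits v control, CR1 | Home visits v Afini, CR1 | Afini v control, CR1 | Home visits v control, CR2-type + Satterthwaite |
|---|---|---|---|---|
| 72/20/72; 15, equal | 6.0% | 6.3% | 5.1% | 4.9% |
| 72/20/72; 15, SD 5 | 6.3% | 6.5% | 5.0% | 5.1% |
| 67/19/78; 15, SD 5 | 6.4% | 6.8% | 5.0% | 5.3% |

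Repeat simulations at these inputs gave 5.9% to 6.9% for home visits v control.

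**Step 4. Covariate-adjusted model.** With province, 10 individual and 6 cluster-level covariates and size SD 5, two sets of simulations (5,000 and 8,004 trials) gave 6.8% to 7.5% for home visits v control under CR1. With province alone the rate was 6.5–6.7%. In the 8,004-trial set, Afini v control was 5.9–6.0%, and CR2 with Satterthwaite df gave 4.8–4.9% (home visits) and 5.0–5.2% (Afini). The number of covariates is an assumption.

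**Step 5. Constrained randomisation.** Choosing the best of 1000 allocations on six cluster covariates (2,000 trials, CR1, home visits v control) gave:

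| Between-cluster variance explained by the balancing covariates (assumed) | Unadjusted | Adjusted for them |
|---|---|---|
| 0% | 6.0% | 6.0% |
| 30% | 4.7% | 6.5% |
| 60% | 2.8% | 6.7% |

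**Step 6. Outside the protocol's inputs.** With cluster-size SD 10, the CR1 rate is about 7–8%. With SD 15 it is about 8–8.5%. With SD 15 and doubled between-cluster variance in the home-visit arm it is 9.0%, and with SD 20 (CV 1.33) it is 9.8%. CR2-type rates are 5.6–6.0% at SD 10 and 6.2–6.7% at SD 15.

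**The case against.** The strongest reply is that the article never says the uncorrected form will be used. CR2 and similar estimators are themselves cluster-robust, so the remedy is compatible with the sentence as written, and the variant may be fixed in an analysis plan that is not shown. This stands as a limit on the claim: no error has been shown to have been made. It does not remove the point. The article names its variance method and signals no correction, and that method in its usual form does not hold its level for a powered comparison.

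The second reply is that constrained randomisation compensates. It can, but only in the unadjusted model and only as far as the balancing covariates predict outcome. The adjusted model, also planned, stays at about 6–7%.

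The third is that 99% power makes the issue immaterial. That power assumes a true effect of 0.5 SD. It says nothing about interval width or about smaller effects on secondary outcomes.

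Three stronger readings are tempting and not supported:
- A reader might infer an error rate near 10%. That needs a cluster-size CV of about 1.3 where the protocol states 0.33. The mix of urban and rural communities does not by itself supply such a spread.
- A reader might take the larger home-visit SEs in Table 4 as proof of bias (for CREDI, 0.163/0.066 = 2.5 against √(67/19) = 1.9 from cluster numbers alone). Other rows are at or below 1.9 (mother's age 0.48/0.26 = 1.8; health card 1.0), and a larger reported SE does not show that SEs are underestimated.
- A reader might extend the point to the 20-cluster top-up comparison. That is an ancillary contrast within the Afini arm, and no claim is made about it here.

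**Conclusion.** The concern holds in modest form. If the usual cluster-robust SE is referred to t(163), home-visit contrasts run at about 6–7% instead of 5%, and up to about 7.5% with many covariates. In the equal-size case the intervals are about 5% too narrow. Afini versus control is essentially unaffected without covariates (about 5%) and only slightly affected with many (about 6%). Using 72/20/72 or 67/19/78 clusters hardly changes the answer.

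This rests on a two-sided test, normal outcomes, and the protocol's ICC and cluster-size spread. The finding is clearest for the adjusted model. For the unadjusted model, the actual rate depends on how well the balancing covariates predict development, which the document does not say; it may be above or below 5%. This is a cheap improvement to the planned inference, not a flaw that threatens the trial.

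**What to change.** In Statistical Analysis, state that home-visit contrasts, and for consistency all contrasts, use a bias-reduced (CR2) cluster-robust variance with Satterthwaite degrees of freedom, or a wild cluster bootstrap. State also that the main models adjust for the province strata and the covariates used to constrain the randomisation. Re-randomisation inference that repeats the best-of-1000 selection can serve as an optional check.

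The cost is a sentence or two and a software option. Home-visit intervals become about 5% wider in the equal-size case, with power about 99% at 0.5 SD before the correction. At the protocol's cluster-size spread, CR2 brings the level back to about 5%. If cluster sizes turn out much more variable, CR2 removes only part of the excess (6.2–6.7% at SD 15), and the re-randomisation check becomes more useful.
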